## STUDY SITE AND POPULATION

### 7.1. Study site

#### 7.1.1. Population-based clusters

SCALE will be implemented in the geographically-defined catchment population of 315 community health workers (CHW) in the high-density and peri-urban residential areas of Blantyre City. CHW catchment areas have been grouped to form 72 clusters with a population of ~4,400 adult residents each (~320,000 adults total). CHW catchment areas and study population was defined by a city-wide brief enumeration with Blantyre DHO in 2015.

The study population is served by 11 Government Primary Care clinics (Bangwe, Chileka, Chilomoni, Limbe, Makhetha, Mbayani, Ndirande, Soche Maternity, South Lunzu, Zingwangwa). Adult HIV prevalence is ~18% and the prevalence of active tuberculosis ~1,000 per 100,000 adults. On-site TB diagnostics available through the routine clinic services include sputum microscopy, with some clinics also having Xpert MTB/Rif and digital chest radiography. All clinics offer point-of-care HIV testing, and immediate ART under the Malawi National Guidelines.

**Figure: Satellite map image of proposed SCALE clusters**

[figure not shown]

#### 7.1.2. Enhanced surveillance of routinely diagnosed TB patients in Blantyre

In collaboration with Blantyre District Health Office (DHO), place of residence (GPS coordinates) and national TB programme data will be collected on all (~2,500 per year) TB

patients into an electronic database, together with a sputum specimen for TB microscopy and culture.

These Electronic TB Register records will be used to assign cluster-resident status (yes/no; cluster number and trial arm) for all registering TB patients during this trial, allowing cluster-level TB case-notification rates to be calculated.

For the purposes of this protocol, MLW will work with Blantyre DHO to adapt the current paper-based Presumptive TB Register, used to record patients being investigated for TB and the results of microbiological tests, into an Electronic Register that allows place of residence GPS coordinates to be captured, enabling investigation of cluster-level rates of TB investigations at primary care level (Appendix 4.3a&b Consent, Appendix 4.5a&b Patient Information Sheet and Appendix 4.4 CRF). MLW will also work with Chiradzulu DHO to add Chiradzulu District Hospital to the Electronic Register, since it has been identified that approximately 34% of patients who registered for TB treatment there in 2017-2019 came from the Blantyre urban area.

Qualitative in-depth interviews will be carried out with purposively selected patients being investigated for TB at primary care level because of cough, aiming to identify cues to action (Appendix 4.1a&b Consent forms, Appendix 4.6a&b participant information sheets and Appendix 4.8 topic guide).

## **7.2. Study Population**

Different populations will be selected for the 2 main phases of the trial (pre-intervention survey and an intervention phase).

The following participants will be recruited for the different stages of the study.

- 15,500 adults selected for the pre-intervention TB and HIV survey
- An estimated 10,000 symptomatic ACF intervention participants

## **7.3. Inclusion criteria**

**Inclusion criteria for the pre-intervention prevalence survey: -**

- Aged 18 years or older
- Resident of an intervention or non-intervention cluster
- Able and willing to provide written (or witnessed) informed consent
- Intending to remain within Blantyre City for at least the next 8 weeks
- Willing to have radiological screening for TB (with abdominal screening for women of child bearing age)

**Inclusion criteria for the ACF intervention: -**

- Aged 18 years or older
- Resident of an intervention cluster
- Reported cough for 2 weeks or longer
- Able and willing to provide written (or witnessed) informed consent
- Willing to provide sputum for TB testing

## 7.4. Exclusion criteria

### Exclusion criteria for the ACF intervention

- Currently on TB treatment

## 7.5. Identification of participants and recruitment

**Pre-intervention prevalence survey:** participants will be recruited from their households, following a preliminary visit by a research assistant to explain the purpose of the study and ask for permission to book a convenient appointment for informed consent and study procedures.

All investigations will be carried out within the community, with no need to travel unless the participant is diagnosed with HIV, TB, or has an abnormal chest radiograph that requires referral for further investigations or treatment.

Pre-intervention survey participants will be recruited using random sampling based on satellite-map images.

Participants (or the Parents/Legal Guardians of participating children) meeting inclusion criteria will be provided with oral and written information about the study by the research assistant (Appendix 3.12a&b flyer and Appendix 3.14a&b information sheet) and will be invited to provide written informed consent to participate in the study (Appendix 3.4a&b consent form). Participants who are illiterate will be asked to provide a thumbprint confirmation of consent, which will be observed and recorded by a witness independent of the study team. Completed consent forms will be securely stored as trial source documents within a trial folder.

**ACF intervention participants:** participants will be recruited from their households, following brief door-to-door enquiry for chronic cough among any household member. Participants will be provided with oral and written information about the study by the research assistant (Appendix 2.1a&b information sheet and consent form) and will be invited to provide written informed consent to participate in the study. Participants who are illiterate will be asked to provide a thumbprint confirmation of consent, which will be observed and recorded by a witness independent of the study team. For participants with reported cough who are not present, the information sheet and consent form (Appendix 2.1a&b) will be left for them to read/have read to them and complete the form for return to the research assistant, along with the sputum pots.

For community-based HIV self-testing, which (unlike sputum collection) is being provided face-to-face, oral consent documented by a thumbprint will be used, in line with national policy and legislation (Appendix 2.2 a&b oral consent and Appendix 2.3 a&b thumbprint consent form).

## **8. RANDOMISATION AND BLINDING**

### **8.1. Randomisation**

The unit of randomisation is the cluster.

Randomisation (1:1 by arm) will be conducted at a public meeting, using random selection of one number from a previously prepared list of 999 randomly selected allocations generated by the trial statistician using a computer programme.

Randomisation will be constrained to avoid extreme differences in geographical distribution between the two arms, and to provide balance in the following variables: -

- Mean distance from cluster centres to the nearest health clinic
- TB case-notification rates as captured by the Blantyre District TB Officers
- Clusters that have received ACF in a previous study.

### **8.2. Blinding**

Because of the nature of the study and the interventions offered, it will not be possible to blind participants or research assistants to allocation groups.

Nevertheless, steps will be taken to ensure that the investigators, including the Principal Investigator and Trial Statistician will remain blinded to allocation groups until database lock preceding final analysis. No unblinded interim analysis will be conducted.

## 9. OUTCOMES AND OUTCOME EVALUATION

Evaluation of the primary outcome will use data from: -

- Blantyre District Electronic TB Register (captured by routine District Health Office staff)

### 9.1. Primary and secondary outcomes

The **primary outcome** will compare between arms

1. **The rate of treatment for microbiologically-confirmed TB (per 1000 adult residents per year) during 3 months starting from the first the ACF intervention**, defined by entry into the District Health Office Electronic TB Treatment Register and laboratory records, with cluster resident status of registering TB patients defined by Global Positioning System (GPS) coordinates for place of residence captured by a satellite map application (ePAL) in routine use by Blantyre District TB Officers.

# Table of objectives, outcomes and pre-planned analyses

| SCALE                                           | Objectives                                                                                                                                                                                                                                                                                                                                                                                                              | Outcome Measures/Endpoints                                                                                                                                                                                                                                                                                                                                                                                                                                                                                                                                                    |
|-------------------------------------------------|-------------------------------------------------------------------------------------------------------------------------------------------------------------------------------------------------------------------------------------------------------------------------------------------------------------------------------------------------------------------------------------------------------------------------|-------------------------------------------------------------------------------------------------------------------------------------------------------------------------------------------------------------------------------------------------------------------------------------------------------------------------------------------------------------------------------------------------------------------------------------------------------------------------------------------------------------------------------------------------------------------------------|
| 1. Primary Outcome                              | 
To determine the impact of TB-ACF on population-level:
 
2.1 Rates of adult registration for microbiologically-confirmed TB
                                                                                                                                                                                                                                                                                 | 
To compare between randomisation arms:
 
2.1 The rate of treatment (per 1000 adult residents per year) during the 12 months starting from the first ACF intervention, defined by entry into the District Health Office TB Treatment Register and laboratory records
                                                                                                                                                                                                                                                                                               |
| 3 Other pre-planned analyses                    | 
To investigate the impact of TB-ACF on population-level:
 
3.1 Demand for routine TB testing services
 
To determine the impact of provider-initiated HIV self-testing for TB-ACF participants on:
 
3.2 Numbers of newly diagnosed HIV-positive participants, and numbers subsequently linking into HIV care
 
3.3 Numbers of participants diagnosed with TB using sputum microscopy
 | 
To compare between randomisation arms:
 
3.1 The rate (per 1000 adult cluster residents p.a.) of investigation for TB, defined by entry into the “Presumptive TB Register” in selected routine TB Registration Facilities
 
Within clusters randomised to the ACF-arm only, to document rates (per 1000 adult cluster residents p.a.) of:
 
3.2 New diagnosis of HIV made by the ACF team using OraQuick, with follow-up for confirmatory testing and ART initiation
 
3.3 New diagnosis of TB made by the ACF team using microscopy
 |
| 4. Economic and mathematical modelling analyses | 
4.1 to determine the costs
 
 
per adult screened with microscopy during ACF
 
per smear+ve TB patient detected by the ACF team
 
per additional adult investigated for TB by the routine health system
 
per additional adult diagnosed with TB by the routine health system
 
likely final scale-up programme costs
 
                  | 
4.1 Costing of ACF from the provider-perspective. Denominators will use records from the ACF team, and routine health system data collected by trial arm under the extended TB surveillance system.
 
4.2 Costing of HIV self-testing for HIV-positive clients to the TB-ACF, with denominators obtained from ACF team and facility records
                                                                                                                                                                                                                       |

|                                    |                                                                                                                                                                                                                                                                                                                                                                                        |                                                                                                                               |
|------------------------------------|----------------------------------------------------------------------------------------------------------------------------------------------------------------------------------------------------------------------------------------------------------------------------------------------------------------------------------------------------------------------------------------|-------------------------------------------------------------------------------------------------------------------------------|
|                                    | 
4.2 to determine the incremental costs of adding HIV to TB ACF
 
 
• per adult screened for HIV by the ACF team
 
• per adult with HIV detected by the ACF team
 
• per adult started on ART
 
 
4.3 to estimate the cost-effectiveness per new TB infection, TB case, and TB death averted by TB and TB+HIV ACF
 | 
4.3 Fully costed mathematical modelling of the TB-ACF intervention with and without additional HIV testing components.
 |
| 5. Transmission modelling analyses | 
5.1 To determine the fraction of Blantyre TB transmission attributable to health facility and HIV care clinic exposure
 
5.2 To investigate the potential epidemiological impact of spatially-targeted TB control interventions and improve infection control and prevention at health facilities and HIV care clinics
                                                     | 
5.1 Transmission modelling of genomic and TB epidemiological data
                                                      |

## 9.2. Additional pre-planned analyses

Additional pre-planned analyses are summarised in the above Table, and will include stratified sub-group analyses by gender, intended to provide better understanding of: -

- the underlying epidemiology of undiagnosed TB and HIV in Blantyre, and how this is affected by ACF as well as by secular trends due to TB and HIV Programme activities and the natural history of the HIV epidemic in Malawi
- the mechanism by which ACF may leads to change in health seeking behaviour
- the costs, cost effectiveness, and projected impact of ACF for TB and HIV on underlying TB epidemiology
- the fraction of TB transmission attributable to health centre and HIV care clinic exposure, and the potential epidemiological benefits of targeted control interventions.

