## 5. BACKGROUND AND RATIONALE

### 5.1. Tuberculosis (TB) in high HIV prevalence settings

#### 5.1.1. Burden of TB disease

TB has been the leading cause of adult deaths from an infectious disease, globally, since 2011, with an estimated 10.0 million new TB cases and 1.6 million TB deaths, including 900 thousand cases and 300 thousand deaths in people living with HIV (PLHIV), in 2017 (1). HIV infection greatly increases the risk of progression from TB infection to TB disease, and also increases the risk of death when TB disease does occur. Because of the regional magnitude of the HIV epidemic, Southern Africa has the highest TB incidence of any global region, with an estimated 84% of all HIV-related TB deaths, globally (1,2).

Prospects for TB control in Africa have changed dramatically in the last 15 years with the highly successful scale-up of antiretroviral (ART) services and global health initiatives for funding TB and HIV programmes (2,3). However, there is still no accurate but low-cost TB test that can be reliably delivered at the point-of-care to diagnose pulmonary disease (4-5). Accessing TB diagnosis remains highly problematic, notably so for adult men who account for most TB cases and deaths but are not as well served as women by TB or HIV programmes (1,2,5-8). This maintains high prevalence of undiagnosed TB (>1% prevalence in urban Blantyre in 2013-14), and hence transmission rates, within communities. Of note, most transmission events occur to casual contacts, limiting the effectiveness of contact tracing strategies, and most TB in high transmission settings results from recently acquired TB infection (9).

Without control of ongoing TB transmission, the full potential of ART and preventive therapy for HIV-positive individuals may not be realized for decades: rapid declines in TB incidence in this region require combined prevention strategies including improved case-finding and treatment (10,11). In Malawi, for example, smear-positive TB case-notifications declined by 16% over a 12 year period when ART coverage (proportion of HIV-infected people retained on ART) increased from <0.5% to 41%, and have declined further since then (12) but are unlikely to the WHO EndTB strategy targets endorsed for 2022 and 2030 unless the large TB-testing gap can be reduced, including for men (13-15).

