## 7. TRIAL DESIGN

SCALE is a cluster-randomised trial of TB/HIV active case-finding with constrained randomization (1:1 ratio) of 72 clusters of ~4,400 adults per cluster, with boundaries defined by community health worker catchment areas

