**Figure 1. Original study design.**

[figure not shown]

*Previously undefined abbreviations:* SOC= Standard of Care; k= thousand; mos= months

**Clusters randomised to the ACF intervention arm** will receive 1 round of brief door-to-door enquiry for chronic cough, repeated after 10 months, with staggered cluster initiation over 9 months. Health promotion messaging will be provided at the time of ACF, through leafleting and door-to-door interactions at the time of brief enquiry for chronic cough.

**All clusters (Enhanced Standard of Care):** Irrespective of randomisation, each facility in the study area will be provided with one study staff member (community/environmental health worker) responsible for facilitating identification of attendees with cough for TB investigations and basic infection control; receiving TB or HIV positive clients referred following ACF; and assisting District TB Officers to register patients being investigated for TB, with a special focus on men.

**Outcomes will be evaluated for months 1-3 from ACF initiation** using routine case-notification data for TB case-notification rates.

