## 14. STATISTICS

### 14.1. Sample size justification

Sample sizes were initially calculated assuming a decline from the last National TB Prevalence Survey in 2013-14 given that there has been case-finding activity since then. However, the interim results from a **pre-intervention survey** show greater than anticipated decline (target of 14,511 participants will give precision of +/- 2.5 around an assumed true prevalence of 900 per 100,000 adults, assuming design effect of 1.5 from random household sampling. The increase to 15,500 allows for wastage from e.g. unreadable Xray/contaminated cultures).

Sample size calculations and statistical analyses will use established approaches for cluster-randomised trials.

The **primary trial outcome** has been changed from self-reported testing outcome to TB case notification.

For this, we assume an annual case-notification of adult microbiologically-confirmed TB to be in the range of 70 to 100 per 100,000 adults for the standard of care clusters, based on current data and trends.

An adult population of ~150,000 per arm followed over 12 months will then provide power to detect a 44% to 56% increase in microbiologically confirmed TB if  $k = 0.3$  to  $0.4$ .

Analysis will use standard methods appropriate for cluster-randomised trials, with adjustment for pre-intervention rates of adult microbiologically-confirmed TB.

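### The gender analysis is planned only as separate strata; a single arm-by-gender contrast should be pre-specified for the between-arm outcomes

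*Combined protocol and SAP*

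**What the plan says.** Section 9.2 states that the additional pre-planned analyses "will include stratified sub-group analyses by gender", "intended to provide better understanding of" several topics, among them how the epidemiology of undiagnosed TB and HIV is changed by ACF. Gender is the only subgroup named. No interaction test, ratio of rate ratios or other comparison between the sexes appears anywhere. Section 9.2 does not say which outcomes are stratified. It points to the table in section 9.1, where item 3.1 (rate of TB investigation) is compared between arms and items 3.2 and 3.3 are measured in the ACF arm only.

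Gender has a visible place in the rationale. Section 5.1.1 speaks of "adult men who account for most TB cases and deaths but are not as well served as women" by TB and HIV programmes. Section 7 gives every facility, in both arms, a staff member whose duties include "assisting District TB Officers to register patients being investigated for TB, with a special focus on men".

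Section 14.2 defers analytic detail to a statistical analysis plan still to be written. The design figures are in sections 7 and 14.1: "constrained randomization (1:1 ratio) of 72 clusters of ~4,400 adults per cluster", a control rate "in the range of 70 to 100 per 100,000 adults for the standard of care clusters", and "An adult population of ~150,000 per arm followed over 12 months will then provide power to detect a 44% to 56% increase" with k of 0.3 to 0.4. The text of section 9.1 measures the primary outcome "during 3 months starting from the first the ACF intervention". The table in the same section and the sample size paragraph use 12 months.

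**The concern.** A stratified analysis yields two arm comparisons, one per sex. Whether the effect differs between men and women is a question about the contrast of those two estimates, and neither comparison answers it alone. Splitting the cases also lowers power in each stratum to a middling level, where one significant and one non-significant result is a common outcome even if the true effects are equal. Readers told that men are poorly served will look for a gender difference, and two p-values side by side invite them to see one. At stake is a spurious statement that ACF helps one gender and not the other, in a trial meant to inform policy.

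**Working it through.** **Inputs.** From the protocol: 36 clusters per arm (72 allocated 1:1); 150,000 adults per arm; control rate λ0 of 70–100 per 100,000 per year; k = 0.3–0.4; rate ratio (RR) 1.44–1.56. Assumed: two-sided 5%, 80% power, 50–65% of cases in men (section 5.1.1 says most cases are in men but gives no figure), between none and all of the cluster effect shared by the sexes, and no gain from adjusting for pre-intervention rates.

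**Step 1: reproduce the plan's figure.** For unmatched clusters,

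c = 1 + (z_α/2 + z_β)² × [(λ0 + λ1)/y + k²(λ0² + λ1²)] / (λ1 − λ0)²,

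with y = 150,000/36 = 4,166.7 person-years per cluster and (1.96 + 0.84)² ≈ 7.85.

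- λ0 = 0.00100, RR 1.44, k = 0.3: [5.86×10⁻⁷ + 2.77×10⁻⁷]/1.936×10⁻⁷ = 4.45, so c = 1 + 7.85 × 4.45 ≈ 36.0.
- λ0 = 0.00070, RR 1.56, k = 0.4: [4.30×10⁻⁷ + 2.69×10⁻⁷]/1.537×10⁻⁷ = 4.55, so c ≈ 36.7. Power with 36 clusters is 79.2%.

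The stated 44–56% is therefore an 80%-power figure.

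**Step 2: power within one sex.** A stratum holding a fraction f of cases has its Poisson term divided by f:

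power = Φ( (λ1 − λ0)/√{[(λ0 + λ1)/(f·y) + k²(λ0² + λ1²)]/35} − 1.96 ).

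For f = 0.5, λ0 = 0.00100, RR 1.44, k = 0.3:
- 12 months: variance (11.71×10⁻⁷ + 2.77×10⁻⁷)/35 = 4.14×10⁻⁸, SE 2.03×10⁻⁴, ratio 2.16, power 0.58.
- 3 months (y ÷ 4): variance (46.85×10⁻⁷ + 2.77×10⁻⁷)/35 = 1.42×10⁻⁷, SE 3.77×10⁻⁴, ratio 1.17, power 0.21.

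**Step 3: chance that exactly one sex is significant, identical effect.** If the two tests are independent, this is p_m(1 − p_w) + p_w(1 − p_m).
- 12 months: 2 × 0.58 × 0.42 = 0.49.
- 3 months: 2 × 0.21 × 0.79 ≈ 0.33 (0.34 before rounding).
- No effect, counting significance in favour of ACF only: 2 × 0.025 × 0.975 = 0.05.

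Simulation covers the other case shares and correlation between the sexes (Poisson counts, lognormal cluster effects, cluster-level t-tests, 20,000 trials per scenario):

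| True effect, same in both sexes | Window | Exactly one sex significant |
|---|---|---|
| RR 1.44–1.56, cluster effect fully shared | 12 months | 41–47% |
| RR 1.44–1.56, none shared | 12 months | 46–52% |
| RR 1.44–1.56 | 3 months | 31–36% |
| RR about 1.84–2.06 (80% overall power) | 3 months | 47–51% |
| RR 2.0, mid-range inputs | 3 months | 48–50% |
| RR 2.0, mid-range inputs | 12 months | 5% |
| None | either | 5% |

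Mid-range means 85 per 100,000, k = 0.35 and 60% of cases in men. A simulation with gamma cluster effects and 4,400 adults per cluster gave 39–46% for the 12-month design effects and 47–50% for RR 1.84–2.06 over 3 months.

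**Step 4: the contrast.** A cluster-level test of the ratio of rate ratios wrongly declared a gender difference in 4.8–5.2% of trials. Its standard error on the log scale was 0.214–0.291 over 12 months. The ratio detectable with 80% power is exp(2.8 × SE): exp(0.599) = 1.8 to exp(0.815) = 2.3. Over 3 months the SE was 0.437–0.558, giving exp(1.224) = 3.4 to exp(1.562) = 4.8.

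**Step 5: sparsity.** Over 3 months a control cluster expects 0.00070 × 4,166.7 × 0.25 = 0.73 to 0.00100 × 4,166.7 × 0.25 = 1.04 cases. With 60% in men, the Poisson chance of zero cases in at least one sex is 1 − (1 − e^(−0.6m))(1 − e^(−0.4m)), where m is the expected count. This gives 91% at m = 0.73 and 84% at m = 1.04.

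**The case against.** The protocol sets no rule that benefit will be judged sex by sex. It offers the strata as an aid to understanding, commits to established cluster-trial methods, and leaves detail to a later plan. That stands: the fault is an omission, and no wrong decision rule is written. A reader might infer that the trial is likely to claim benefit in one gender only. The documents do not support that, because they plan no such claim and discordant results are not the majority outcome in most scenarios.

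A reader might also take 40–50% as a general error rate. It is close to the peak of a curve. It applies when the true effect is about the size that the whole trial has 80% power to detect, and it falls to about 5% with no effect. It is also about 5% at a 12-month doubling, the size of increase that section 5.1.2 reports for earlier ACF in Blantyre. The rate ratios of 1.84–2.06 are not in the protocol; they are what 80% power would need over 3 months.

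Three further objections stand. Section 9.2 may mean only the outcomes in its table, and for items 3.2 and 3.3, with one arm, no contrast is possible. Nothing shows that men and women share a cluster effect, so it cannot be assumed to cancel; a pooled-count test that assumes it does would reject wrongly in about 7–8.5% of 12-month trials if the effects were independent. Lastly, the staff focus on men in section 7 applies to both arms, so it does not itself suggest that the effect varies by gender.

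Low power of the contrast does not favour separate tests. The wide interval shows what the trial cannot resolve, and two separate p-values hide it.

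**Conclusion.** The point holds as a minor one. The stated method cannot answer whether the ACF effect differs by gender, and the contrast that can is missing. Used side by side on the primary outcome with equal true effects, the separate tests would disagree in about 40–50% of trials at the 12-month design effect, about one third with that effect over 3 months, about 47–50% with RR near 1.84–2.06 over 3 months, and about 5% with no effect or a 12-month doubling. The contrast errs in about 5%. The figures rest on application to the primary outcome, 50–65% of cases in men and two-sided 5% tests, none of which the protocol states. The analysis is exploratory and the primary comparison is unaffected.

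**What to change.** In section 9.2 and the statistical analysis plan:

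- State which outcomes the gender analysis covers. For those compared between arms (the primary outcome and item 3.1), pre-specify one arm-by-gender contrast from a count model with arm × gender. The model should allow for clustering, including cluster effects that may differ by sex.
- Report the ratio of rate ratios with its 95% CI. Show the sex-specific estimates as descriptive, and base no claim of a gender difference on separate p-values.
- Do not use within-cluster male-to-female ratios. Over 3 months most clusters would have no cases in at least one sex, leaving the ratio zero or undefined.
- Confirm that the enumeration records sex, so that adult denominators exist by sex; the protocol does not say so. If they do not exist, state the assumption that the population sex ratio is balanced between arms.
- Acknowledge the low power in advance.

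The cost is a few sentences and one model, with no change to the design. The drawback is a wide interval that will often leave the question open.
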